#### Data Collection: Primary and Secondary Psychosocial Outcomes

Patient-caregiver dyad data will be collected at 3 time points—baseline (T_0_) completed prerandomization, first follow-up (T_1_) at 12 weeks post baseline, and second follow-up (T_2_) at 24 weeks post baseline. All data will be completed by the dyads (regardless of allocation) using the FOCUSau software platform, whereby they will complete a suite of internet-based questionnaires. The platform enables the application of data validation rules to ensure that required data are entered or that an annotation is provided to explain any missing data. The FOCUSau platform automatically generates a unique ID number used by the dyad to log into the platform. Data collection will be completed separately by the patient and caregiver (regardless of allocation). The data collection points, outcomes, and measures have been selected in accordance with those used in the aforementioned EU trial to enhance international comparison and potential generalizability [39].

The list of variables and associated measures to be completed by the dyad are summarized in Table 1 and are as follows, for the primary outcomes—emotional well-being (10 items describing emotional functioning from the European Organization for Research and Treatment of Cancer (EORTC) The European Organisation for Research and Treatment of Cancer Core Quality of Life Questionnaire (QLQ-C30) [55,56] and self-efficacy (The Lewis’ Cancer self-efficacy scale [57]); for the secondary outcomes—QoL of patients—EORTC QLQ-palliative care [58], 2 social functioning items (#26, 27) plus 1 item about overall health (#29) from the EORTC QLQ-C30, social well-being scale from Functional Assessment of Cancer Therapy-General (FACT-G)—and family caregivers (The Caregiver Quality of Life Index-Cancer [59]), appraisal of illness (Benefits of illness scale [60]), coping (Brief cope [61]), and dyad communication (Ways of giving support questionnaire [62] plus 1 item from the Dyadic Coping Inventory).

In addition, we will administer a sociodemographic questionnaire at baseline (T_0_) and a modified version of the Eastern Cooperative Oncology Group (ECOG) Performance Status Assessment [63] (response option 5 “death” removed as not relevant for this study).

**Table 1 table1:** Trial data collection measures.

Objective and outcome or variable			Instrument	Timing		
				T_0_: Before randomization	T_1_:T_0_ + 12 weeks	T_2_: T_0_ + 24 weeks
**Outcome measures used for the primary outcomes**						
	**Psychosocial effectiveness**					
		Emotional well-being	For patients: EORTC^a^ QLQ-C30^b^ emotional function items (10 items) For caregivers: EORTC QLQ-C30 item emotional function scale (10 items)	✓	✓	✓
		Self-efficacy	For patients and caregivers: the Lewis’ Cancer self-efficacy scale (17 items)	✓	✓	✓
**Outcome measures used for the secondary outcomes**						
	**Psychosocial effectiveness**					
		Quality of life	For patients: EORTC QLQ-C15-PAL (23 items) + 2 social function items + 2 items about overall health from EORTC QLQ-C30; social well-being scale from the FACT-G^c^ (6 items) For caregivers: the Caregiver Quality of Life Index-Cancer (CQOLC; 35 items)	✓	✓	✓
		Appraisal of illness	For patients and caregivers: benefits of illness scale (5 items)	✓	✓	✓
		Coping	For patients and caregivers: a shortened version of Brief Cope (20 items)	✓	✓	✓
		Communication	For patients and caregivers: the “Active engagement scale” (5 items) from the “Ways of giving support questionnaire.” Three scales (10 items) from the “Dyadic Coping Inventory”: “Stress communication by oneself,” “Stress communication by partner,” and “Evaluation of dyadic coping”	✓	✓	✓
		Level of functioning	For patients (4 items): modified version of Eastern Cooperative Oncology Group (ECOG) Performance Status Assessment (item 5 “death” removed)	✓	✓	✓
	**Cost-effectiveness**					
		Health economic measures	For patients (23 items) 17 and for caregivers (14 items): client Services Receipt Inventory (CSRI) including use of hospital versus in-patient palliative EoL^d^ care and the use of informal care or services provided outside of the health care system (to be completed by caregivers) and modified to reduce overlap with Medicare data	✓	✓	✓
		Primary outcome expressed as cost per participant with a meaningful change in well-being or self-efficacy for the intervention compared with control	For patients and caregivers: EQ-5D and EQ-5D-5L (5 items)	✓	✓	✓
		Secondary outcomes expressed as cost per quality adjusted life year for the intervention compared with control	For patients and caregivers: Services Australia data—use of outpatient medical and pharmaceutical services	✓	✓	✓
	**Implementability**					
		Acceptability	For patients and for caregivers (intervention group): Theoretical Framework of Acceptability (TFA) survey (9 items)—perceptions based on info provided and actual after completion	✓	✓	✓
		Acceptability	For patients and for caregivers (control group) 1: Theoretical Framework of Acceptability (TFA) survey (9 items) perceptions based on info provided only	✓		
		Acceptability	For patients and for caregivers (intervention group only): qualitative (interviews) to explore acceptability and barriers and enablers to uptake of FOCUSau by dyads, the latter informed by the Theoretical Domains Framework of behavior		✓	
		Satisfaction with intervention	For patients and for caregivers (intervention group): FOCUS items asking about experience and satisfaction with the intervention (intervention group only) For patients (12 items) For caregivers (12 items)		✓	✓
		Uptake	Study log: recruitment data including reasons for accepting or declining participation, sociodemographic profile of invited dyads, and capacity to reach vulnerable populations (with lower socioeconomic status, cultural minorities, and from rural or remote locations)	✓	✓	✓
		Intervention fidelity	Study log: communication between trial managers and participants, whether for technical problem-solving or for other reasons. Aspects of adherence (intervention as received) are built into the FOCUSau intervention. Completion rates of individual FOCUSau sessions	✓	✓	✓
		Technical feasibility	Interviews or focus groups with health IT experts: data and infrastructure standards adherence, system architecture for interoperability or integration with electronic patient records, and extensibility and scalability potential	✓	✓	✓
	**Other characteristics**					
		Sociodemographic characteristics	For patients (14 items) and for caregivers (15 items): sex, age, relationship status, living situation, children, educational level, employment status, income, financial difficulties, medical insurance, ethnicity, and dyad’s relationship	✓		
		Patient level of functioning	For patients (1 item): modified version of Eastern Cooperative Oncology Group (ECOG) Performance Status Assessment (response option 5 “death” removed as not relevant)	✓	✓	✓

^a^EORTC: European Organization for Research and Treatment of Cancer.

^b^QLQ-C30: The European Organisation for Research and Treatment of Cancer Core Quality of Life Questionnaire.

^c^FACT-G: Functional Assessment of Cancer Therapy-General.

^d^EoL: end of life.

#### Data Collection: Health Services Use

The impact on health care costs of FOCUSau will be determined by analyzing patterns and costs of health care use, including the costs of administering the intervention. Information will be collected on the time required to administer FOCUSau (per patient and overall). The impact of FOCUSau and usual care on health care services’ use will be assessed by consenting participants for access to their Medicare (Australian Government health services) data (to obtain information on the use of outpatient medical and pharmaceutical services) and using the Client Services Receipt Inventory (CSRI) [64]; modified to reduce overlap with Medicare data. The CSRI will also allow us to explore the use of hospital versus inpatient palliative EoL care, and the use of informal care or services provided outside of the health care system (to be completed by caregivers).

#### Data Collection: Implementability

Table 1 also outlines data to be collected to measure factors related to implementability of the intervention. This will include piloting and administering a new acceptability questionnaire [44]. Interview topic guides (1 for patients; a parallel guide for caregivers) will be informed by the Theoretical Domains Framework (TDF) of behavior change [65].

#### Sample Size

A predetermined strict fixed sequence (FS) procedure defines prospectively hierarchical ordering of the primary end points; (1) emotional well-being and (2) self-efficacy. Testing of null hypotheses proceeds according to their hierarchical order; that is, H(1)0 is tested first at a significance level of 5%, and if H(1)0 is rejected then H(2)0 is tested at the same significance level, otherwise H(2)0 is not tested at all. The strict FS approach has the highest power for testing the first hypothesis (outcome: emotional well-being) compared to the other methods, as it does not save any portion of α for testing the later hypothesis. The reference mean value from EORTC for all patients with cancer, stage III-IV is 71.5 (SD 23.8). To maintain rigorous control over type I errors due to multiple comparisons, the α level is set at .025 instead of the more common .05. This adjustment accounts for the multiple comparisons required in the study, including comparisons between a control group and 2 participant groups (patients and caregivers). We set the statistical power at 0.80. The expected difference between the control group and the intervention arm in the primary outcomes is SD 0.375 at T_1_ (12 weeks). With these parameters, 173 dyads are needed in each arm (ie, 346 dyads in total). Anticipating a maximum 80% retention rate at T_1_ (US FOCUS retention was 86% [38]) we will require approximately 433 dyads to be recruited. An enrollment rate of 55% of those eligible was achieved in a prior digital health FOCUS study from 2014 [38]; however, we anticipate this will be higher for FOCUSaus (estimating 70%) given the internet is much more widely available now and our digital recruitment approach, meaning that we will need to identify approximately 618 dyads who meet eligibility criteria. Evidence also suggests that recruitment rates can increase when a digital health intervention is offered [18]. To meet these targets the CTS has calculated that approximately 6 referral sites will be required complemented by our aforementioned self-referral strategy.

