#### Data Analysis

The effectiveness of FOCUSau will be compared with the standard care (control group) for each participant population (patients or caregivers). Our hypotheses will be tested using a mixed model (per participant population) with the T_1_ measurement values for emotional well-being and self-efficacy as primary outcomes using a significance level of α=.025. These mixed models will be implemented using SPSS (IBM Corp) for Windows (version 27.0; Microsoft Corp) and R (R Core Team) with the recruitment centers treated as a random effect and the randomization groups as predictor variables. As per the FS procedure, the null hypotheses of the second primary end point (self-efficacy) will only be tested if a significant result is found for the first primary end point (emotional well-being). Additionally, we will incorporate other factors identified in the literature as potentially predictive by including them as covariates in the mixed models. We will perform analyses on both “intention-to-treat” and per-protocol principles. To interpret the magnitude of the effects for the different outcomes, we will estimate effect sizes (Cohen *d*). Our analysis will encompass all primary and secondary outcomes. Primary end points, including emotional well-being and self-efficacy measured at T_1_, will be analyzed first. Following that, secondary end points, comprising outcomes measured at T_1_ that are not primary end points, as well as all outcomes measured at T_2_ (occurring 24 weeks from T_0_), will be assessed. This approach allows for a comprehensive evaluation, including the examination of longer-term effects.

The robustness and validity of the results will be explored using sensitivity analyses by varying the parameter inputs (including sensitivity to the use of values for missing observations). The analysis will be conducted within trial period; the potential to extrapolate results over the longer term will be assessed based on the proportion of patients alive at the end of follow-up.

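### The fixed-sequence rule tests the primary end points at 5%, while the same section and Data Analysis set .025 for the same tests

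*Protocol article*

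**What the plan says.** The protocol article gives the level of the primary tests in three places.

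- Sample Size, fixed-sequence rule: "H(1)0 is tested first at a significance level of 5" per cent. The rule continues: "if H(1)0 is rejected then H(2)0 is tested at the same significance level". As written, this is a per-test level of 5% for emotional well-being and then for self-efficacy.
- Sample Size, a few sentences later: "the α level is set at .025 instead of the more common .05". The reason given is multiple comparisons, "including comparisons between a control group and 2 participant groups (patients and caregivers".
- Data Analysis: "Our hypotheses will be tested using a mixed model (per participant population", with the T1 values of the two end points "as primary outcomes using a significance level of α=.025".

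The gate is repeated under Data Analysis: self-efficacy "will only be tested if a significant result is found for the first primary end point (emotional well-being". That sentence restates neither the level nor the population in which the result must be significant.

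**The concern.** The two levels govern the same decisions: the T1 tests of emotional well-being and self-efficacy. Take p = .03 for emotional well-being in patients. Under the fixed-sequence sentence the null is rejected and self-efficacy is tested. Under Data Analysis the null stands and self-efficacy is not tested. The level thus decides both whether a primary result is positive and whether the second primary end point is tested at all.

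The two levels also differ in what they protect. A fixed sequence controls error across the two end points within one population. It does nothing across two populations, each with its own model. Applying 5% in each would leave uncorrected the very multiplicity that the article names as its reason for .025.

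**Working it through.** **Inputs.** Per-test level 5% (fixed-sequence rule) or .025 (later in Sample Size, and Data Analysis). Two populations, one model each. Two ordered end points per population. Sidedness is not stated; two-sided is assumed here. The independence figures in steps 2 and 4 depend only on the per-test level.

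**Step 1: error within one population.** If the emotional well-being null is true, any false rejection must begin there, so the error of the sequence is at most α. If that null is false, only self-efficacy can be falsely rejected, again with probability at most α. Each population's sequence therefore has error at most α.

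**Step 2: error over patients and caregivers.** With all nulls true and independent tests, the family-wise error is 1 − (1 − α)²:

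- 5% each: 1 − 0.95² = 0.0975, or 9.75% (upper bound 2 × 5% = 10%).
- .025 each: 1 − 0.975² = 0.0494, or 4.94% (upper bound 2 × 2.5% = 5%).

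The members of a dyad are related, so the two test statistics may be correlated. The article gives no correlation; the values below are assumptions (bivariate normal, two-sided):

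| Correlation | 5% each | .025 each |
|---|---|---|
| 0.3 | 9.51% | 4.84% |
| 0.5 | 9.07% | 4.65% |
| 0.7 | 8.35% | 4.30% |

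Over this range the 5% version stays well above 5%, and the .025 version stays below it.

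**Step 3: how often the two rules would disagree.** With the planned effect of 0.375 SD and 173 per arm, the power of a single test is 93.7% at two-sided .05 and 89.4% at two-sided .025. The difference, 93.7% − 89.4% = 4.3%, is the chance that one test falls between the two levels.

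**Step 4: the gate, if it were shared.** Suppose success on emotional well-being in either population opened self-efficacy in both, every test being at .025. The error then exceeds 5% only if emotional well-being truly differs in exactly one population and both self-efficacy nulls are true. Three true nulls can then be tested, and the error is at most 1 − 0.975³ = 0.0731, or 7.3% (independence), which requires the gate to open with certainty. With the gate opening at the 89.4% power above, it is 1 − 0.975 × (0.894 × 0.975² + 0.106) = 0.068, or 6.8%. If all nulls are true, or if emotional well-being truly differs in both populations, the error is at most 4.94%.

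**Step 5: can the planned size show which level was meant?** It cannot. With n = 2(z + 0.842)²/0.375² per arm for "We set the statistical power at 0.80", two-sided .025 (z = 2.241) gives 136 and two-sided .05 (z = 1.960) gives 112. The stated 173 matches neither.

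**The case against.** The strongest reply is that the plan already settles the level. The .025 is presented as a replacement for .05, carries a reason and is repeated in the section that governs the analysis. The 5% stands in a passage explaining how a fixed sequence works and looks like an uncorrected sentence. On that view p = .04 fails, and the 9.75% belongs to a procedure that the plan does not intend. Much of this stands. A reader might infer that p-values between .025 and .05 have no defined meaning, or that the trial runs at nearly 10% error. The document supports neither, because its rationale and analysis section both favour .025.

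What does not stand is that the passages already agree. No sentence says that the 5% is a total split into .025 per population; the rule says the first null is tested at 5%. Reading .025 as one-sided and 5% as two-sided does not help either, because .025 is introduced as a reduction from .05 for multiple comparisons. Nor is this a detail left to an analysis plan: the article states the level, and states it two ways.

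A reader might also infer that success in one population opens self-efficacy in both. The gate sentence permits that reading but does not state it. Since the models are specified per population, a gate within each population is the more natural reading.

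**Conclusion.** The contradiction is real and sits in the current text: one sentence sets 5% and two set .025 for the same primary tests. It is a wrong sentence to be corrected, since the plan's own reasoning leads to .025. If the 5% sentence were followed in each population, error over patients and caregivers would roughly double. That conclusion assumes that the two populations form one family, as the article's own rationale does; the correlated figures also assume two-sided tests and a chosen correlation.

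The gate is a secondary clarification. Its cost is bounded by about 7.3%, and only in the one configuration described. The contradiction does not bear on the sample size. The mismatch between 173 and the stated inputs is a separate matter on which this point does not depend.

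**What to change.** In the fixed-sequence sentence under Sample Size, replace the 5% by: *.025 in each population (5% overall across patients and caregivers)*. State whether the tests are one-sided or two-sided.

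Add one clarifying sentence there or under Data Analysis: *The sequence runs separately within patients and within caregivers; a significant result for emotional well-being opens the test of self-efficacy only in the same population.*

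The cost is one or two sentences. Sample size, data collection and models are unchanged. The correction should be on record before any comparison by arm is seen, so that the level cannot appear to have been chosen afterwards.

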**Methods:**

FOCUS will be adapted prior to trial commencement, using an iterative stakeholder feedback process to create FOCUSau. To examine the efficacy and cost-effectiveness of FOCUSau and assess its acceptability, feasibility, and scalability, we will undertake a hybrid type 1 implementation study consisting of a phase 3 (clinical effectiveness) trial along with an observational implementation study. Participants will include patients with cancer who are older than 18 years, able to access the internet, and able to identify a primary support person or caregiver who can also be approached for participation. The sample size consists of 173 dyads in each arm (ie, 346 dyads in total). Patient-caregiver dyad data will be collected at 3 time points—baseline (T_0_) completed prerandomization; first follow-up (T_1_; N=346) at 12 weeks post baseline; and second follow-up (T_2_) at 24 weeks post baseline.

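### The stated alpha of .025, power of 0.80 and difference of 0.375 SD give 137 dyads per arm, not the 173 attributed to them; 173 analysed per arm has about 89% power

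*Protocol article*

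**What the plan says.** The Sample Size section gives three inputs. On the significance level: "the α level is set at .025 instead of the more common .05", which the Data Analysis section repeats for the models fitted in each population ("using a significance level of α=.025"). On power: "We set the statistical power at 0.80". On the effect: "The expected difference between the control group and the intervention arm in the primary outcomes is SD 0.375 at T_1_ (12 weeks". From these it draws its result: "With these parameters, 173 dyads are needed in each arm (ie, 346 dyads in total". It then allows for 80% retention at 12 weeks ("we will require approximately 433 dyads to be recruited") and for 70% enrolment, which brings the eligible dyads to be identified to about 618.

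The abstract says "The sample size consists of 173 dyads in each arm (ie, 346 dyads in total" and attaches N=346 to the first follow-up. It does not mention 433. Sidedness is not stated. No design effect, correlation or joint-power target is given. Earlier in the Sample Size section the fixed-sequence rule uses another level: "H(1)0 is tested first at a significance level of 5" percent.

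**The concern.** The section presents 173 as the direct product of three listed inputs, so a reader should be able to reproduce it. It is well above what those inputs give. The figures of 433 and 618, and the estimate of about six referral sites, all rest on it. If 173 is wrong for the stated design, the error carries through to the recruitment target. If 173 is right, the power, the effect size or the definition of power is misdescribed. It also matters if recruitment is slow: the sponsor would then need to know what power a smaller number gives, and the article as written does not give a sound answer.

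**Working it through.** **Inputs.** Difference d = 0.375 SD, alpha = .025, power = 0.80, two equal arms, 80% retention (Sample Size section). Patients and caregivers are analysed separately (Data Analysis section), so each dyad contributes one person to each comparison. The reference SD of 23.8 cancels because the effect is in SD units. Two-sided testing is my assumption; the other reading is shown too.

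**Trying to reproduce 173.** For two means, n per arm = 2(z₁₋α/₂ + z₁₋β)² / d².

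- Two-sided .025: 2(2.2414 + 0.8416)² / 0.375² = 135.2, so 136. The t test gives 136.4, so 137.
- Two-sided .05, which is the same as one-sided .025: 2(1.9600 + 0.8416)² / 0.375² = 111.6, so 112. The t test gives 112.6, so 113.

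Neither reading gives 173, and the .05 reading moves further away. The excess over 137 is 173/137 = 1.26.

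**Power if 173 per arm are analysed.** The noncentrality is 0.375 × √(173/2) = 3.488. Power at two-sided .025 is Φ(3.488 − 2.241) = 0.894, or 0.891 by the t test. With 173 per arm, 80% power is reached at 0.333 SD (t test; 0.331 normal).

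**The later steps.** 346/0.80 = 432.5, so 433; and 433/0.70 = 618.6, against the stated 618. These are consistent with each other, so the discrepancy lies in 173 itself. Starting from 137 per arm, 274/0.80 = 342.5, so 343 dyads to recruit (344 if each arm is rounded up: 137/0.80 = 171.25, so 172).

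**Where 173 might come from.** None of these is stated in the article.

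| Possible source | n per arm |
|---|---|
| 20% loss already included: 137/0.80 = 171.25 | 172 |
| 80% power to win two independent tests at .025, each needing √0.80 = 0.894: 2(2.2414 + 1.2504)²/0.375² = 173.4 | 174 (t test 175) |
| Two-sided alpha of .025/3, power 0.80 | 173 (t test 174) |
| Effect of about 0.33 SD, power 0.80 | about 173 |
| Design effect of 173/137 | 1.26 needed |

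**The case against.** The strongest defence is that 173 may be a sound number with an incomplete description. The section opens with two ordered primary end points and states one expected difference for both. A target of 80% power to win two independent tests needs 174 to 175 per arm, almost the stated figure. On that reading 80% would be right and nothing is counted twice. This stands as a possibility, and it is why no cause should be asserted. It does not rescue the text, which attributes 173 to the listed parameters and mentions no joint target.

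A reader might infer that the 20% loss has been applied twice, because 346 × 0.80 = 277, about 138 per arm, has roughly 80% power. The documents do not establish this. Working forward, 137/0.80 gives 172, not 173, and the joint-power reading lands about as close. A reader might also infer that 346 is really the number randomised. The text points the other way: the abstract puts N=346 at the first follow-up, and the Sample Size section puts 433 at recruitment.

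It is also fair to say that the error is conservative. With 173 analysed per arm, each single test has more power than claimed. The primary analysis and its type I error are not affected by this point. The clash between 5% and .025 is a separate inconsistency and does not explain 173.

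**Conclusion.** The point holds as a misstated calculation. The stated inputs require 137 dyads per arm (136 by the normal approximation), against 173 stated, an excess of about 26%. If 173 per arm are analysed at alpha .025, power for emotional well-being in each population is about 89%, not 80%.

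This rests on a two-sided test, a plain two-group comparison within each population, and no adjustment for covariates or centre, since the article quantifies none. A one-sided reading widens the gap.

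The cause is open. The figures do not show an underpowered trial. Nor do they show that the surplus of about 90 dyads (433 − 343) is unneeded, because that holds only if 80% power for a single test was the aim.

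**What to change.** Restate the calculation in the Sample Size section so that inputs and result agree, giving the sidedness of the test and any input now missing.

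- If 173 analysed per arm and 433 recruited are kept, state about 89% power per single test at alpha .025. If joint power was the target, say so, name the tests it covers, and give the assumed correlation.
- If the sponsor confirms from its own records that 173 already allowed for 20% loss, correct the 433 and the 618 that follow from it. Without that confirmation the recruitment target should not be cut.
- In the abstract, give 433 as the number to recruit beside 346 at the first follow-up.

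The cost is rewording one paragraph and one line of the abstract, after a check of the original calculation. No extra participants are needed.
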